##### Duration from SSA transfer to RTW

The duration from SSA transfer to RTW is operationalised as the actual duration that the sick-listed worker was under counselling by the front office of the SSA until the end of the sickness benefit. When unemployed and temporary agency workers report themselves sick, first the back office of the SSA is notified. It may take two to four weeks before the front office of the SSA receives the sick report. Only after the front office receives the report can the sickness absence counselling begin. Workers with expired fixed-term contracts (those whose contracts expired while they were sick-listed) will register at the SSA later in the sick leave process than the unemployed and temporary agency workers because the contract workers have an employer at the time of reporting sick. At this registration, the SSA receives all data from the start of the sick leave onwards, from the former employer and occupational health service related to the employer. After expiration of the fixed-term contract, the SSA becomes responsible for the sickness benefit claim, so the actual duration of SSA counselling for this sick-listed worker is shorter then the duration of sick leave. Data are continuously recorded and will be acquired from the SSA database.

##### Number of days of paid employment during follow-up

The number of days of paid employment during the follow-up period will be obtained from both the SSA database and the self-reported information in the questionnaires at 4, 8 and 12 months after the SSA received the sick report.

##### Degree of participation

The degree of participation can vary between being inactive, doing volunteer work, working in a work experience situation (real labour experience without wage) and paid work. The degree of participation will be obtained from both the SSA database and the self-reported information in the questionnaires at 4, 8 and 12 months after the SSA received the sick report (ordinal scale: inactive/volunteer/labour experience/paid work).

##### Psychological complaints

Psychological complaints are measured using the Dutch translation of the General Health Questionnaire-12 (GHQ-12) at baseline, and 4, 8 and 12 months after the SSA received the sick report [30].

##### Self-efficacy for return to work

Self-efficacy as related to work performance after sick leave is measured with a validated RTW self-efficacy questionnaire at baseline, and 4, 8 and 12 months after the SSA received the sick report [31].

##### Costs and benefits from SSA perspective

Costs and benefits from the SSA perspective refer to the incremental costs and benefits of the Brainwork Intervention. Incremental costs are the costs of the Brainwork Intervention minus the costs of the usual care. The incremental benefits are the benefits of the Brainwork Intervention minus the benefits of the usual care. Costs associated with Brainwork are the training and educational costs for the OH professionals, the wage of the OH professionals and the costs of the Brainwork Intervention. Costs for usual care include the wage of the OH professionals and the costs of the interventions if deployed. Benefits for both groups are associated with savings in sickness and unemployment benefit claims. In the context of this study there are only benefits from the SSA perspective if the sick-listed worker returned to paid work after the end of the sickness benefit claim. The ending of the sickness benefit claim by returning to the unemployment benefit is not beneficial for the SSA because the SSA is also responsible for the unemployment benefit claims. Data will be acquired from the SSA database.

An overview of the outcome measures and the measurement instruments used, including a time path for all measurements, is presented in Table 2. Quantitative indicators for process measurement will be obtained from the SSA database.

**Table 2 Tab2:** **Overview of outcome measures and their instruments and time path**

	**Time path**				
	**Baseline**	**4 months**	**8 months**	**12 months**	**Continuous**
	**T0**	**T1**	**T2**	**T3**	**(until 12 months)**
**Data instruments**					
Dutch SSA* Database					X
Questionnaires 1 to 4	1	2	3	4	
**Measurements**					
**Primary outcome**					
Duration of sick leave					X
*(SSA Database)*					
**Secondary outcome**					
Proportion of subjects returned to work at 8 and 12 months *(SSA Database)*			X	X	
Duration from transfer to the SSA until RTW *(SSA Database)*					X
Number of days of paid employment during follow-up		X	X	X	
*(questionnaire and SSA database)*					
Degree of participation		X	X	X	
*(questionnaire and SSA database)*					
Psychological complaints	X	X	X	X	
*(questionnaire)*					
Self-efficacy for return to work	X	X	X	X	
*(questionnaire)*					
Costs and benefits from SSA perspective					X
*(SSA Database)*					

*Dutch SSA = Dutch Social Security Agency.

### Sample size and power analysis

A power analysis was performed to calculate the required number of participants in this study. The mean and standard deviations of the duration of sick leave of all sick-listed workers without an employment contract having psychological problems who registered at the SSA in 2011 were taken as a starting point. Because there are no data available from previous studies on the expected differences, we only calculated how many participants are needed to display any differences in duration of sick leave. The power analysis using program nQuery Advisor showed that 144 participants are needed per group (288 total) to detect a mean difference in duration of sick leave of 40 days. Therefore, we decided to include 300 participants for this study.

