#### Recruitment and training of occupational health professionals

At each SSA office, an existing team of OH professionals is designated as an intervention team and one as a control group team. An OH professional team consists of insurance physicians, vocational rehabilitation counsellors, labour experts, at least one nurse practitioner and secretaries. Instruction and coaching sessions are held for all of the OH professionals on the intervention team. Members of this team also receive a syllabus with detailed information about the Brainwork Intervention, the protocol, practical summaries, flowcharts, a schedule of actions and the registration forms to aid in the application of this new intervention. Furthermore, team members receive a two-day training in motivational interviewing. The training provides the OH professionals with the motivational interviewing skills necessary to activate the sick-listed workers’ participation in the Brainwork Intervention, to initiate positive behavioural changes and to address resistance to change of the sick-listed workers.

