#### Effect evaluation

To assess the effectiveness of the Brainwork Intervention for the primary outcome, a Linear Mixed Models (LMM) analysis of the differences between the average sick leave duration (in days) in the intervention and control group will be performed. Therefore, a model with group as fixed factor and the vocational rehabilitation counsellor of the SSA at a primary hierarchical level and the participants at a secondary hierarchical level (where appropriate) will be built. For all participants who have not returned to work after 1 year of follow-up, the value of 365 days of sickness absence will be imputed.

For the secondary outcomes, excepting costs and benefits, LMM analysis for continuous outcomes and Generalized Linear Mixed Models analysis for dichotomous/ordinal outcomes will be performed. Therefore, a model with group as fixed factor and the vocational rehabilitation counsellor of the SSA at a primary hierarchical level and the participants at a secondary hierarchical level (where appropriate) will be built. In the case of differences in the ratios between the types of workers (unemployed and temporary agency versus expired fixed-term contract) due to attrition, a correction for the differences will be performed by including type of worker as a covariate in the analysis.

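### The 144 per group for a 40-day difference shows no allowance for counsellor clustering, and 300 participants cover it only if the design effect is at most about 1.04

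*Protocol article*

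**What the plan says.** **Sample size (Protocol article, Sample size and power analysis).** The starting point is "The mean and standard deviations of the duration of sick leave of all sick-listed workers without an employment contract" who had psychological problems and registered with the agency in 2011. The result is that "144 participants are needed per group (288 total) to detect a mean difference in duration of sick leave of 40 days". The section ends: "Therefore, we decided to include 300 participants for this study". It gives no value for the SD, alpha, sidedness or power, and it mentions no ICC, caseload, number of counsellors or design effect. It also says that no earlier data on the expected difference were available.

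**Primary model (Effect evaluation).** Sick leave duration is compared with a linear mixed model that has group as fixed factor and "the vocational rehabilitation counsellor of the SSA at a primary hierarchical level", with participants at the level below. The structure is qualified as applying where appropriate. Anyone not back at work after one year is given 365 days.

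**Who treats whom (Recruitment and training of occupational health professionals).** At each office "an existing team of OH professionals is designated as an intervention team and one as a control group team". Vocational rehabilitation counsellors are members of these teams. There are three offices, hence six teams, three per arm.

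**Allocation and follow-up.** Workers are allocated individually within office (Randomisation). No loss of primary outcome data is expected (Primary outcome).

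**The concern.** The sample size section describes a comparison of two groups of independent workers. The analysis section foresees that workers of one counsellor may resemble each other on the same outcome. The two parts do not match.

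Individual allocation would make this harmless if each counsellor saw workers from both arms, because counsellor differences would then largely cancel. The team structure prevents that. With a separate team for each arm, a counsellor's tendency towards longer or shorter claims falls wholly on one arm and adds to the variance of the treatment contrast.

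At stake is how the result is read. The trial is presented as sized for 40 days. If the detectable difference is really larger, a null result would be taken as stronger evidence against a 40-day effect than it is.

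**Working it through.** **1. Reproducing 144 per group.** For two independent means, n per group = 2(z_α + z_β)² SD² / Δ², with Δ = 40 and n = 144. Since SD, alpha and power are not stated, solve for the SD: SD = 40 × √(144/2) / (z_α + z_β) = 339.4 / (z_α + z_β).

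- Two-sided 5%, 80% power (assumed): 339.4 / 2.802 = 121.1 days.
- Two-sided 5%, 90% power (assumed): 339.4 / 3.242 = 104.7 days.

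Several input pairs return 144, so the figure can be neither confirmed nor refuted. With no clustering, 300 participants give 81.6% power (80% target) or 91.1% (90% target).

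**2. What the rounding-up can absorb.** For m workers per counsellor and intraclass correlation ICC, the design effect is DE = 1 + (m − 1) × ICC. The required total is 288 × DE, so 300 suffices only if DE ≤ 300/288 = 1.042. That means ICC ≤ 0.042 / (m − 1):

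- m = 5: ICC ≤ 0.0104
- m = 12.5: ICC ≤ 0.0036
- m = 25: ICC ≤ 0.0017

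No primary outcome loss is expected, so all 12 extra participants count towards this margin.

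**3. Detectable difference and power at 300.** The difference detectable at the planned power is 40 × √(288 × DE / 300). It does not depend on whether 80% or 90% was planned. Power for 40 days uses an effective 150/DE per group. Caseload and ICC are assumptions; 5 to 25 workers each corresponds to 60 down to 12 counsellors in all.

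| m | ICC | DE | Total needed | Detectable difference (days) | Power if 80% planned | Power if 90% planned |
|---|---|---|---|---|---|---|
| 5 | 0.01 | 1.04 | 300 | 40.0 | 80.1% | 90.0% |
| 5 | 0.02 | 1.08 | 312 | 40.7 | 78.6% | 88.9% |
| 5 | 0.05 | 1.20 | 346 | 42.9 | 74.2% | 85.5% |
| 12.5 | 0.01 | 1.11 | 322 | 41.4 | 77.3% | 88.0% |
| 12.5 | 0.02 | 1.23 | 355 | 43.5 | 73.2% | 84.7% |
| 12.5 | 0.05 | 1.58 | 454 | 49.2 | 62.5% | 75.1% |
| 25 | 0.01 | 1.24 | 358 | 43.6 | 72.8% | 84.4% |
| 25 | 0.02 | 1.48 | 427 | 47.7 | 65.2% | 77.6% |
| 25 | 0.05 | 2.20 | 634 | 58.1 | 48.7% | 60.7% |

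Worked row (m = 12.5, ICC 0.02): DE = 1 + 11.5 × 0.02 = 1.23; total 288 × 1.23 = 354.2, so 355; detectable difference 40 × √(0.96 × 1.23) = 43.5 days.

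These powers use the normal approximation. With a t reference on (counsellors − 2) degrees of freedom, that row (24 counsellors) falls to 69.3% or 81.3%.

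**The case against.** The strongest reply is that nothing shows 300 to be too few. ICC and caseload appear nowhere in the document. With an ICC near zero the detectable difference is 39.2 days, and with 5 workers per counsellor and an ICC of 0.01 it is 40.0. If 144 was set at 90% power, power stays above 80% over much of the table. The counsellor level is to be fitted only where appropriate. With SD, alpha and power unstated, it cannot be proved that the calculation contains no hidden allowance. All of this stands. A reader might infer that 300 participants cannot deliver the 40 days; the document does not support that. What remains is that the section describes no allowance, while the model and the team structure call for one.

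Three further inferences are also tempting and should not be drawn.

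- **That the 365-day cap shrinks the 40 days and ruins power.** Benefit can run for two years, but the sample size section does not say that the 2011 durations were uncapped. An uncapped exponential scenario with means 200 and 160 does not fit the plan: at 80% power it would need 7.849 × (200² + 160²) / 40² ≈ 322 per group, not 144.
- **That type I error is inflated by a known amount.** Team and arm coincide within each office, and a counsellor effect cannot remove a team difference. Any figure for its effect would need a between-team SD that the document does not give. It is a limitation to state, not a quantified error.
- **That the trial contrast should be corrected by subtracting a 2011 difference between teams.** That assumes stable teams and case mix, and adds noise from a non-randomised comparison.

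**Conclusion.** The point holds in a conditional form. As written, the 144 per group for 40 days does not match the trial's own analysis model and team structure, because no allowance for counsellor clustering is shown. The planned 300 cover the 40-day target only up to a design effect of about 1.04. Over 5 to 25 workers per counsellor and an ICC of 0.01 to 0.05, the detectable difference at the planned power is about 40 to 58 days, so the consequence ranges from nil to substantial.

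This rests on the assumed caseload and ICC range, on a two-sided 5% test for the power figures, on equal caseloads, and on each counsellor working in one team only. It does not ask for detail that belongs in an analysis plan: the article itself states the number, its basis, the model and the team structure, and these do not fit together.

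**What to change.** In Sample size and power analysis:

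- State the SD, alpha, sidedness and planned power behind the 144.
- Give the expected number of counsellors per arm and a counsellor ICC. Take the ICC from the 2011 register if it identifies counsellors; otherwise use an assumed range and label it as such.
- Take the SD from the same register on the 365-day-capped scale that the primary analysis uses, or say that this was already done.
- Replace the 40 days with the difference detectable with 300 participants, including the design effect.

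In the Discussion, state as a limitation that team and arm coincide within each office.

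The cost is a text change and one rerun on data already used for planning. No extra participants are needed. The downside is a somewhat less favourable stated figure. Since the section concedes that no earlier data on the expected difference were available, restating the 40 days gives up no externally supported target.

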### Data analysis

All statistical analyses will be performed at worker’s level according to the intention-to-treat principle. To check the success of the quasi randomisation procedure similarities in the descriptive statistics will be determined, comparing the baseline measurements of both groups. If necessary, the main analyses will be adjusted for prognostic dissimilarities. For those aspects of the protocol which were fixed for all participants, such as personal attention given by the OH professional to the sick-listed worker through face-to-face contact within five working days after the SSA received the sick report, or timely referral of the worker to the external intervention partner, the protocol deviations will be analyzed. To assess the presence of bias due to protocol deviations, the results of the intention-to-treat analyses will be compared to per-protocol analyses.

#### Effect evaluation

To assess the effectiveness of the Brainwork Intervention for the primary outcome, a Linear Mixed Models (LMM) analysis of the differences between the average sick leave duration (in days) in the intervention and control group will be performed. Therefore, a model with group as fixed factor and the vocational rehabilitation counsellor of the SSA at a primary hierarchical level and the participants at a secondary hierarchical level (where appropriate) will be built. For all participants who have not returned to work after 1 year of follow-up, the value of 365 days of sickness absence will be imputed.

For the secondary outcomes, excepting costs and benefits, LMM analysis for continuous outcomes and Generalized Linear Mixed Models analysis for dichotomous/ordinal outcomes will be performed. Therefore, a model with group as fixed factor and the vocational rehabilitation counsellor of the SSA at a primary hierarchical level and the participants at a secondary hierarchical level (where appropriate) will be built. In the case of differences in the ratios between the types of workers (unemployed and temporary agency versus expired fixed-term contract) due to attrition, a correction for the differences will be performed by including type of worker as a covariate in the analysis.

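### For GHQ-12 and return-to-work self-efficacy the article prespecifies group as the only fixed term; adding the collected baseline score and time would gain precision and separate the visits at almost no cost

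*Protocol article*

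**What the plan says.** Protocol article, Effect evaluation: for all secondary outcomes other than costs and benefits, "LMM analysis for continuous outcomes and Generalized Linear Mixed Models analysis for dichotomous/ordinal outcomes will be performed". The model is "a model with group as fixed factor and the vocational rehabilitation counsellor of the SSA at a primary hierarchical level". A second level, for the individual worker, is added only where that is judged fitting. The same model sentence is used for the primary outcome, which is one register-based duration per worker.

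The two scales have a different data structure. Psychological complaints are measured with the "General Health Questionnaire-12 (GHQ-12) at baseline, and 4, 8 and 12 months after the SSA received the sick report". Self-efficacy is measured with a "validated RTW self-efficacy questionnaire at baseline, and 4, 8 and 12 months after the SSA received the sick report". Table 2 confirms T0 to T3 for both.

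Two covariate provisions exist, both conditional:
- Data analysis: after the groups have been compared at baseline, "If necessary, the main analyses will be adjusted for prognostic dissimilarities".
- Effect evaluation: worker type is added if attrition has changed the ratio of worker types between the groups. Worker type is the pre-stratification factor in the Randomisation section.

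Neither provision introduces time, and neither commits in advance to the baseline score. The article does not say whether the T0 score is an outcome row, a covariate or neither.

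**The concern.** A model suited to one value per worker has been carried over to scales with one baseline and three follow-up scores. A baseline score of the same scale is normally a strong predictor of the later scores, and its value for precision does not depend on whether the arms happen to differ at baseline. Making adjustment conditional on observed imbalance therefore gives up precision when the arms look alike, and makes the model data-dependent when they do not.

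Without time and group-by-time terms, the three follow-ups yield one pooled contrast, so an early effect that fades cannot be told from a late one. These outcomes also come from posted questionnaires sent only to workers who consented, so visits will be missing. Workers enter while sick-listed, so scores are likely to improve over time. If the mix of returned visits differs between arms, part of that improvement can appear as a group effect.

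At stake are the precision and interpretability of two secondary outcomes.

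**Working it through.** **The plan's own figure.** The article gives no precision or power figure for these scales. Its 144 per group concerns sick-leave duration and does not enter here.

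**Inputs.** From the documents: one baseline and three follow-up scores; 300 participants planned, so about 150 per arm. Assumed, because the documents give no values: scores analysed as continuous with unit variance, exchangeable correlation r between any two visits, complete data, no counsellor clustering. The sample size n per arm cancels in the variance ratios.

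**1. One follow-up visit.** Baseline adjustment multiplies the variance by 1 − r².
- r = 0.4: 1 − 0.16 = 0.84, so 16% removed; 1/0.84 = 1.19, equivalent to 19% more respondents.
- r = 0.6: 1 − 0.36 = 0.64, so 36% removed; 1/0.64 = 1.56, equivalent to 56% more.

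**2. Average of three follow-up visits.** Variance of the group contrast:
- group only: (2/n)(1 + 2r)/3
- with baseline score: (2/n)[(1 + 2r)/3 − r²]

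| r | group only, ×(2/n) | adjusted, ×(2/n) | ratio adjusted/group only | removed |
|---|---|---|---|---|
| 0.3 | 0.533 | 0.443 | 0.83 | 17% |
| 0.4 | 0.600 | 0.440 | 0.73 | 27% |
| 0.5 | 0.667 | 0.417 | 0.63 | 38% |
| 0.6 | 0.733 | 0.373 | 0.51 | 49% |
| 0.7 | 0.800 | 0.310 | 0.39 | 61% |

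Inverting the end rows, the group-only variance is 1.2 (r = 0.3) to 2.6 (r = 0.7) times the adjusted one.

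**3. If T0 were also an outcome row.** With four equally weighted visits and a constant effect d after baseline, the group coefficient estimates (0 + d + d + d)/4 = 0.75d, with variance (2/n)(1 + 3r)/4.

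**4. Illustration at r = 0.5, n = 150 per arm, assumed d = 0.30.** Power is taken as Φ(estimate/SE − 1.96).
- Follow-up visits, group only: SE = √(0.01333 × 0.667) = 0.094; power 0.89.
- Follow-up visits with baseline score: SE = √(0.01333 × 0.417) = 0.075; power 0.98.
- All four visits, group only: expected estimate 0.225; SE = √(0.01333 × 0.625) = 0.091; power 0.69.

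A check with 100 simulated trials (random-intercept model, true effect −0.30, common improvement over time) gave mean estimates of −0.307 (SE 0.094), −0.295 (SE 0.075; this model also had time terms) and −0.236 (SE 0.091), in the same order. These agree with the formulas. Real questionnaire response will be lower than 150 per arm, so the power values show direction only.

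**5. Omitted time.** With balanced, complete data each arm has the same mix of visits, so a common trend cancels from the group contrast. With missing visits, a simple pooled mean carries an extra term Σ(p₁ₖ − p₀ₖ)μₖ, where pₖ is the share of an arm's returned forms that belong to visit k and μₖ is the common mean at that visit. It vanishes when the visit mix is equal in both arms. The documents give no response rates, so no size can be attached to it.

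**The case against.** The strongest reply is that this is a condensed article. Its model sentence is a generic template that also covers outcomes with no baseline score or repeated scores, and naming group as a fixed factor does not say that there is no other. Time and baseline terms may stand in a full analysis plan that is not shown. This stands as a caution, and any such plan should be checked first. It does not remove the point, because the article is not silent: it fixes the model's fixed part and hierarchy, and makes both covariate provisions conditional. Those published choices are worse than an equally short alternative.

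A reader might infer that the planned model understates the effect by 25%. The documents do not support that. It would need T0 to be an outcome row, and no section says so; the only stated use of baseline measurements is the balance check and possible adjustment. A reader might also infer that leaving out time biases the comparison in itself. It does not in balanced, complete data.

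It is also fair to say that adjustment is not wholly absent. The Data analysis section could bring the baseline score in if the arms differ, although it speaks of the main analyses and waits for the data.

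Finally, the baseline form is posted after inclusion, while the intervention's first face-to-face contact is due within five working days of the sick report. Some baseline scores may therefore already reflect early contact, and adjusting for them could remove part of the effect. This stands and shapes the fix.

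**Conclusion.** The point holds as a worthwhile, low-cost improvement confined to two secondary outcomes. Group is the only fixed term prespecified for scales with a baseline and three follow-up scores. On the likeliest reading, with follow-up scores as the outcomes, the cost is precision and not bias: 16 to 36% of the variance at a single visit, or about 27 to 49% for the three-visit average, could be removed if the baseline-to-follow-up correlation is 0.4 to 0.6. The correlations, exchangeability and complete data are assumptions. Dilution to about 75% of the effect would follow only if T0 were analysed as an outcome row. The missing time terms leave effects by visit unseparated and expose the contrast to bias only if missingness by visit differs between arms. The primary outcome and the sample size are unaffected.

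**What to change.** For GHQ-12 and return-to-work self-efficacy, replace the shared model sentence with one that:
- takes the 4, 8 and 12 month scores as outcomes and states that T0 is a covariate, not an outcome row;
- prespecifies fixed effects for group, time, group-by-time, baseline score, worker type and office, whatever the observed balance or attrition;
- includes participant and counsellor as random effects;
- reports the group contrast with its confidence interval at each visit. If one visit is to lead, name it in advance; the article does not favour one.

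Record the date on which each baseline form is completed, and add a sensitivity analysis without the baseline covariate, because early intervention contact may precede that form.

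The cost is a change of wording and one extra date field. The scores, worker type and office are already available, and no further participants or measurements are needed.
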